### Randomisation

Participants will be assigned to either the intervention or control group based on their pre-existing haemodialysis schedule. The dialysis unit operates two main haemodialysis therapy groups: group 1 (Monday, Wednesday, Friday) and group 2 (Tuesday, Thursday, Saturday). Each main group is further divided into three sub-sessions based on the time of day: morning, afternoon, and evening. This results in a total of six possible haemodialysis therapy routes:

Route 1: Monday, Wednesday, Friday; Morning.Route 2: Monday, Wednesday, Friday; Afternoon.Route 3: Monday, Wednesday, Friday; Evening.Route 4: Tuesday, Thursday, Saturday; Morning.Route 5: Tuesday, Thursday, Saturday; Afternoon.Route 6: Tuesday, Thursday, Saturday; Evening.

In Phase 3 of this pseudo-randomised controlled study with a parallel design, participants in each of the six routes will be allocated to either the intervention or control arm. To minimise potential bias and contamination between groups, all participants in a given route (e.g., Monday, Wednesday, Friday; Morning/Afternoon/Evening) will be assigned to the same study arm. This approach ensures that intervention and control group participants will not have overlapping haemodialysis schedules, reducing the likelihood of communication and influencing between groups.

The allocation of each route to either the intervention or control arm will be determined by the research team. This pseudo-randomisation method, while not truly random at the individual level, offers a pragmatic approach to group allocation given the scheduling constraints of the haemodialysis unit and the need to minimize potential bias between study arms.

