### Intervention implementation and practical considerations

Participants will be instructed to use their non-fistula/graft arm for interacting with the tablet during CGT to avoid any potential complications. All tablets will have stands to minimise arm movement if required.

Regarding the timing of dialysis shifts, we acknowledge that early morning shifts may pose challenges. To address this, we will ensure that the CGT apps are designed with adjustable brightness and volume settings to accommodate patient comfort at different times of day.

The involvement of dialysis staff will be minimal to ensure the intervention remains patient-led. Staff responsibilities will include:

Initial setup of tablets (performed by the research team).Providing tablets to patients at the start of their session.Basic troubleshooting if needed (e.g., restarting an app).Collecting tablets at the end of the session.

Staff will receive a brief training session on these responsibilities. We estimate this will require no more than 5–10 min of staff time per patient per session. The research team will be available to address any technical issues that arise.

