No formal power calculation was conducted because this pilot study focuses on evaluating the feasibility and acceptability of using CGT apps in individuals undergoing haemodialysis. The primary goal of this pilot trial is to collect initial data and assess the study procedures rather than testing a specific hypothesis with a predetermined level of statistical power. The results from this pilot study will guide the design and sample size calculation for a future, larger scale definitive randomised controlled trial.

While our sample size limits a detailed analysis of the impact of different dialysis schedules, we will collect data on each participant’s schedule (Monday-Wednesday-Friday or Tuesday-Thursday-Saturday, and shift time). We will conduct exploratory analyses to examine potential associations between schedule and outcomes. This information will be valuable for designing a larger future trial where schedule effects could be more robustly analysed.

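### The allocation rule places no constraint on shift, so a whole shift can fall in one arm; drawing lots within the three shift pairs would prevent that at almost no cost

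*Protocol article*

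**What the plan says.** The Randomisation section of the protocol article describes two day patterns (Monday-Wednesday-Friday and Tuesday-Thursday-Saturday). Within them, "Each main group is further divided into three sub-sessions based on the time of day: morning, afternoon, and evening". Hence "This results in a total of six possible haemodialysis therapy routes", and each shift appears exactly twice, once in each day pattern.

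The allocation rule is that "participants in each of the six routes will be allocated to either the intervention or control arm", and that everyone in a route "will be assigned to the same study arm". The stated reason is that "intervention and control group participants will not have overlapping haemodialysis schedules". On who decides, the section says: "The allocation of each route to either the intervention or control arm will be determined by the research team". It mentions no pairing, no stratification by shift, no random sequence and no number of routes per arm. The section on trial population and recruitment expresses an intention to balance baseline characteristics but attaches no mechanism to it.

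Shift time is mentioned in two other places. The section on intervention implementation says "we acknowledge that early morning shifts may pose challenges" and responds with brightness and volume settings. The Statistical analysis section records each participant's schedule for exploratory analysis and adds: "This information will be valuable for designing a larger future trial where schedule effects could be more robustly analysed". The planned between-arm analysis in that section is an independent ANOVA, and no shift term is named.

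**The concern.** Whole routes are the unit of allocation and there are only six of them, so the choice of routes fixes the mix of shifts in each arm. Nothing in the rule stops the intervention arm from holding both morning routes and the control arm both evening routes.

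If patients on different shifts differ in their scores, in their four-month change, in app use or in retention, that difference would be read as part of the arm difference. For a shift held by one arm only, there would be no comparison of intervention with control within that shift.

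This matters even in a pilot, because the Statistical analysis section intends to use the results to estimate effect sizes and to size a definitive trial. The exploratory schedule analysis would suffer too. Where a shift occurs in one arm only, its contrast with a shift found only in the other arm cannot be told apart from the treatment contrast.

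**Working it through.** **Inputs from the protocol article (Randomisation section).** Two day patterns and three shifts. The protocol's own figure is reproduced: 2 × 3 = 6 routes. The pairs sharing a shift are 1/4 (morning), 2/5 (afternoon) and 3/6 (evening). Planned arm sizes are 30 and 25 (Participant withdrawal section).

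**Assumptions, because the documents give no figure.** Three routes per arm, equal route sizes, and a morning-evening difference of 0.2 to 0.4 SD.

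**Step 1: count the allocations.**
- Ways to give three of six routes to the intervention: C(6,3) = 20.
- Ways in which every shift is present in both arms: one choice per pair, 2³ = 8.
- Ways in which some shift lies wholly in one arm: 20 − 8 = 12, or 12/20 = 60%.
- Direct check of the 12: 3 choices for the shift held wholly by the intervention × 2 for the shift held wholly by control × 2 ways to divide the remaining shift = 12. In each of these, two shifts are unshared and one is shared.
- If the number of routes per arm is left free (both arms non-empty), there are 2⁶ − 2 = 62 allocations. Still only 8 have every shift in both arms, so 54/62 = 87% do not.

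**Step 2: worst case.** Take both morning routes plus one afternoon route against both evening routes plus one afternoon route. With M, A and E the mean outcomes by shift:

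(2M + A)/3 − (2E + A)/3 = (2/3)(M − E)

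- M − E = 0.2 SD gives 0.13 SD.
- M − E = 0.4 SD gives 0.27 SD.

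Morning and evening lie wholly in opposite arms in 2 × 2 = 4 of the 20 splits. If afternoon lies midway between the other two, the remaining 8 unbalanced splits give half as much, (1/3)(M − E), or 0.07 to 0.13 SD.

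**Step 3: yardstick.** Treating patients as independent, the standard error of the arm difference is √(1/30 + 1/25) = 0.27 SD. This ignores any similarity of patients within a route, so it is if anything too small. It also uses 30 and 25, whereas equal routes would give equal arms. It serves only for scale.

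**Step 4: after pairing.** Of the 8 paired allocations, none has a whole shift in one arm. With equal route sizes the shift-related difference between arms is 0. With unequal sizes some remains: if morning supplied 14 of 30 in one arm and 6 of 25 in the other (assumed), a morning effect of 0.5 SD would leave 0.5 × (14/30 − 6/25) = 0.11 SD. In 2 of the 8, all Monday-Wednesday-Friday routes fall in one arm.

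**The case against.** **The gap may be one of reporting.** A journal article condenses the full protocol, and a balance constraint might be stated there. The article does not describe an unbalanced split, and its illustration of a route could be read as moving a whole day group, which would balance shift. This stands in part. However, the article sets out its allocation rule in a dedicated section, speaks of each of six routes being allocated, and gives the choice to the research team. Allocating whole day groups would also tie arm to day pattern. The pairing is offered as an improvement on the stated rule, not as a complaint that detail is absent.

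**A reader might infer that the protocol concedes a shift effect.** It does not. It says that early shifts may be challenging, in the context of patient comfort, and it plans to explore potential associations. It does not say that different kinds of patient attend different shifts.

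**A reader might infer that the distortion could never be removed.** That is too strong. The stated outcomes are changes from baseline, so stable differences between shift populations largely cancel. In every unbalanced three-three split, one shift is still present in both arms. The primary outcome as worded is change within the intervention group, which shift imbalance between arms does not confound. What remains exposed is the between-arm comparison planned under Phase three and in the Statistical analysis section, the comparison of scores at four months in the Outcomes section, and adherence and retention if these depend on shift.

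**The 60% might be read as a risk.** It is a proportion of allocations. The research team chooses, so no probability attaches to it. Under a random draw, mirror-image splits are equally likely and the expected bias is zero; the cost is then chance imbalance, which adds variance.

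**This is a pilot that discloses its limits.** It disclaims hypothesis testing and admits that allocation is not truly random. That limits the seriousness of the point but does not remove it, since the estimates feed the next trial.

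**Conclusion.** The point holds as a cheap, worthwhile improvement to the stated allocation rule. As written, the rule permits a shift to lie wholly in one arm (12 of 20 three-three splits), and the stated between-arm analysis has no shift term to offset it.

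The size of any resulting bias is unknown from the documents. The 0.13 to 0.27 SD figure is a worst case. It rests on an assumed morning-evening difference of 0.2 to 0.4 SD in whatever outcome is compared, on equal route sizes, and on the 4 of 20 splits that put morning and evening in opposite arms. It amounts to between about half and one standard error of the arm difference.

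The documents do not support saying that the trial will be confounded by shift, that a shift effect exists, or that no comparison could be recovered. Nor does pairing guarantee exact balance: it ensures that every shift is represented in both arms.

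**What to change.** Add to the Randomisation section: within each shift (routes 1 and 4 for morning, 2 and 5 for afternoon, 3 and 6 for evening), one route is assigned to the intervention and the other to control by lot. Add to the Statistical analysis section that the between-arm comparison includes shift as a factor.

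The same routes, patients and staff are used, and whole-route separation is kept, because paired routes run on different days and never overlap. The draw within pairs also takes the choice away from the research team.

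Costs and limits:
- Arm totals would follow the route sizes, so 30 and 25 may not be reached exactly.
- Unequal routes leave some shift imbalance. The shift term helps with this, at the price of two degrees of freedom.
- Two of the eight paired allocations place each day pattern wholly in one arm. Drawing only from the other six avoids this and still gives every route an equal chance of either arm (3 of 6). Day pattern then divides 2:1 rather than evenly, which is the best that three pairs allow.

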### Participant withdrawal

Participants have the right to withdraw from treatment and/or the trial at any time. Participants will remain in the trial for follow-up unless they request to fully withdraw. All data up to the point of withdrawal will be stored, after withdrawal participant’s data will be destroyed and will not be included in the final dataset.

In the event of participant withdrawal, the Investigator(s) will promptly explain to the participant that their involvement in the trial will discontinue and explain why.

For Phase two, the focus group/semi-structured interview sessions will be conducted with people who are currently receiving haemodialysis therapy. After receiving feedback from the focus groups/semi-structured interviews, a finalist of CGT apps will be determined to be used during haemodialysis sessions.

Fifty-five people attending haemodialysis therapy will be recruited for Phase three. The intervention arm includes 30 patients to account for up to a 20% potential dropout and ensure at least 25 can complete the study. The control arm will have 25 haemodialysis patients with usual care. All participants will complete assessments at baseline and at approximately four months (± two weeks).

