### Statistical analysis

Given the pilot nature of this study, our sample size is not based on formal power calculations. Instead, it is pragmatically determined by the number of eligible patients in our dialysis unit. The results will be used to estimate effect sizes and inform sample size calculations for a future, full-scale randomised controlled trial.

In Phase three, data will be analysed to test the effect of CGT intervention on the scores of baseline and follow-up assessments. All data analyses will be conducted in IBM SPSS Statistics for Windows, version 27.0 (or higher) software. Data will be directly entered into Microsoft Office Excel spreadsheets (version 2202) by investigators and study staff using all standard data management procedures. Descriptive statistics will be calculated according to the normality assumption, with means and standard deviations reported for normally distributed data, and medians and interquartile ranges reported for non-normally distributed data. Within-group comparisons between baseline and follow-up assessments for primary and secondary measurements will be analysed using repeated-measures analysis of variance (ANOVA). In contrast, independent ANOVA will be used for between-group comparisons. For additional explorative analyses, correlation and regression models can be used to analyse the effects of other factors (e.g. age, gender) on the cognitive decline between the baseline and follow-up assessments.

In addition to the primary and secondary outcome analyses, a sub-group analysis will be performed to explore the potential effects of the CGT intervention based on participants’ baseline memory function and executive function. Participants will be stratified into subgroups based on their performance on the cognitive test scores, and the intervention effects will be compared between these subgroups. This exploratory analysis may help to identify which patients are most likely to benefit from the CGT intervention and guide future research in this area.

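### Arms are formed from six whole dialysis routes, but the between-arm analysis treats patients as independent, so precision is overstated if outcomes correlate at all within a route

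*Protocol article*

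**What the plan says.** The Randomisation section crosses two day groups with three times of day: "This results in a total of six possible haemodialysis therapy routes". Allocation is at that level: "all participants in a given route (e.g., Monday, Wednesday, Friday; Morning/Afternoon/Evening) will be assigned to the same study arm". The arms are not drawn at random: "The allocation of each route to either the intervention or control arm will be determined by the research team". How many routes go to each arm is not stated.

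The numbers are under Participant withdrawal: "Fifty-five people attending haemodialysis therapy will be recruited for Phase three", with 30 in the intervention arm and 25 in the control arm.

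The Statistical analysis section names repeated-measures ANOVA for changes within a group and, for the arms, says that "independent ANOVA will be used for between-group comparisons". Neither method has a route term. The same section allows optional regression on factors such as age and gender. It also records each participant's day group and shift, and plans an exploratory look at schedule against outcome. On later use it says: "The results will be used to estimate effect sizes and inform sample size calculations for a future, full-scale randomised controlled trial".

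**The concern.** The unit of allocation is the route and the unit of analysis is the patient. Independent ANOVA takes its error term from the scatter of patients within arms, as if each patient had been assigned separately. Patients on one route share days and time of day. The protocol itself gives grounds to expect some within-route correlation: it keeps the arms on separate schedules because patients who dialyse together may influence one another, it notes that early morning shifts may be difficult, and it plans to look for associations between schedule and outcome.

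At stake is the precision attached to the arm difference. The Statistical analysis section says the data will be used to test the intervention's effect and that the effect sizes will feed the design of a definitive trial. An estimate that looks more certain than six routes can make it would mislead that step.

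**Working it through.** **Inputs from the protocol article.** Six routes (Randomisation). Total 55, as 30 intervention and 25 control (Participant withdrawal). Patient-level ANOVA between arms (Statistical analysis).

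**Assumptions, because the protocol gives no figure.** ICC from 0 to 0.20; two-sided 5% test; three routes per arm with sizes 10, 10, 10 and 9, 8, 8. A split of two routes against four is tried as well.

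**The plan's own figure.** No power, SD or ICC is stated, so there is no precision figure to reproduce. The one derived number is the intervention arm: 25 × 1.20 = 30. (Strictly, 30 × 0.80 = 24, one short of the 25 completers wanted; that is a separate and minor matter.)

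**Degrees of freedom.** Patients: 55 − 2 = 53, critical t = 2.006. Routes: 6 − 2 = 4, critical t = 2.776. Ratio 2.776 / 2.006 = 1.38.

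**Design effect.** Mean route size m = 55 / 6 = 9.17; DE = 1 + (m − 1) × ICC; interval ratio = √DE × 1.38. Type I error is from 100,000 simulated null trials per ICC value.

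| Assumed ICC | DE | Effective N of 55 | √DE | Interval ratio | Type I error, planned ANOVA | Type I error, t-test on six route means |
|---|---|---|---|---|---|---|
| 0 | 1.00 | 55 | 1.00 | 1.38 | 0.048 | 0.048 |
| 0.01 | 1.08 | 51 | 1.04 | 1.44 | 0.059 | 0.050 |
| 0.02 | 1.16 | 47 | 1.08 | 1.49 | 0.069 | 0.051 |
| 0.05 | 1.41 | 39 | 1.19 | 1.64 | 0.099 | 0.050 |
| 0.10 | 1.82 | 30 | 1.35 | 1.87 | 0.148 | 0.050 |
| 0.20 | 2.63 | 21 | 1.62 | 2.25 | 0.236 | 0.050 |

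In the simulation the true standard error was 1.09, 1.20 and 1.38 times the ANOVA's at ICC 0.02, 0.05 and 0.10, close to √DE.

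**Sensitivity.** With two routes against four, the ANOVA's type I error is 0.105 at ICC 0.05 and 0.163 at 0.10. With 25 completers in each arm and three routes each, it is 0.095 and 0.140.

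**Effect on the patient-level SD.** Each arm spans several routes, so the within-arm residual keeps most of the between-route variance. Its expectation is the within-route variance plus k times the between-route variance, where

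k = [(30 − 300/30) + (25 − 209/25)] / 53 = (20 + 16.64) / 53 = 36.64 / 53 = 0.69.

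The patient-level variance is therefore understated by (1 − 0.69) × ICC: about 0.6%, 1.5% and 3.1% at ICC 0.02, 0.05 and 0.10. For the SD this is about 0.3%, 0.8% and 1.6%.

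**What six routes can say about the ICC.** With 4 and 49 degrees of freedom, an F-based 95% interval taken at the expected F for a true ICC of 0.05 runs from below zero to about 0.55.

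**The case against.** The strongest reply is that this is a pilot. Trial population and recruitment and Statistical analysis both make feasibility the primary aim, the latter disclaims a test at predetermined power, and the Outcomes section ties further work to feasibility and acceptability. No decision rests on a p-value, and the protocol promises neither a significance level nor a confidence interval. This stands, and it lowers the weight of the point. It does not remove it, because the same document says it will test the effect and pass effect sizes forward.

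Second, the protocol gives no ICC. If it were zero, the planned test would be valid. This stands too: every figure above is conditional, and at ICC 0.01 to 0.02 the type I error is only 6% to 7%.

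Third, schedule data are collected and explored. That makes a repair possible but is not one, since an exploratory association leaves the standard error of the arm comparison unchanged. Nor can this be left to an unseen analysis plan: the protocol names its method, and that method does not match its allocation.

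Four stronger readings are tempting and are not supported.

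- A reader might infer that the variance handed to the future trial leaves out the between-route part. It does not; about 69% is retained and the SD is nearly right.
- A reader might charge the whole 1.5 to 1.9-fold widening to ignored correlation. A factor of 1.38 is the change from 53 to 4 degrees of freedom, which applies even at ICC 0. Clustering contributes 1.08, 1.19 and 1.35.
- A reader might argue from the small number of possible route permutations. That needs a stated split of routes and a random allocation, and the protocol provides neither.
- A reader might say the future trial is being denied an ICC that it needs. The protocol does not say that trial will allocate by route, and six routes would give only a very rough value.

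**Conclusion.** The mismatch between allocation and analysis is real and is stated outright in the protocol. For any positive within-route correlation, the planned between-arm ANOVA understates the standard error of the arm difference and is anti-conservative: type I error of about 7%, 10% and 15% at assumed ICCs of 0.02, 0.05 and 0.10, and nominal at zero. What is overstated is the precision of the effect estimate, not materially the SD. These figures assume three routes per arm and 55 analysed patients; the sensitivity runs do not change the picture.

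The point should be fixed, but it does not undermine the pilot's main purpose. It concerns the between-arm comparison. The Outcomes section words the primary outcome as change from baseline within the intervention group, so the figures above do not bear on that contrast.

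**What to change.** In the Statistical analysis section, replace independent ANOVA for the between-arm comparison with a comparison of the six baseline-adjusted route means by a t-test on 4 degrees of freedom. Support it with a mixed model that has a random intercept for route and small-sample degrees of freedom. Route should not be entered as an ordinary fixed effect, because routes are nested within arms and would absorb the arm difference. State how many routes go to each arm; with two against four and unequal route sizes, the test on unweighted route means was conservative in simulation (type I error 0.03 to 0.04).

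Report the arm difference with its 95% interval. Give the ICC with its very wide interval as description only. Say that between-arm results are exploratory and that no claim of significance will be made from six routes.

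The cost is wording. Day group and shift are already to be recorded, and SPSS can fit the model. The visible downside is wider intervals. The change does not cure any bias from the research team choosing each route's arm, which is a separate matter.

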### Trial population and recruitment

The investigators will collaborate with local representatives of KPAs and people within the kidney service to recruit the participants who are currently receiving haemodialysis therapy at the Hull University Teaching Hospitals NHS Trust kidney service. Healthcare professionals at the kidney unit will discuss study participation with the patients before obtaining formal informed consent.

The investigators will give potential participants a letter and the trial participant information sheet. Consent for participation in the trial will be collected via a formal Informed Consent Form authored by the investigators; the consent form will check candidates suitability against both inclusion and exclusion criteria (fit recruitment profile/ confirmation that situations have not changed since recruitment), and outline the specifics of the trial, what activity is included in the intervention sessions (methodology outline) and how both feedback and personal data will be collected and processed. All inclusion and exclusion criteria are given in Table 1. For Phase two, the focus group/semi-structured interview sessions will be conducted with people who meet the same inclusion and exclusion criteria as the main trial participants (Table 1), ensuring consistency in the target population.

**Table 1 Tab1:** Inclusion and exclusion criteria of the proposed trial.

Inclusion criteria	Exclusion criteria
18 years or older	Less than 18 years of age
regular haemodialysis therapy for at least three months	Haemodialysis for less than three months
	Planned kidney transplant within the intervention period
	Active malignancy
	Inability to complete study assessments from the clinical perspective
	Inability to complete the interventions from the clinical perspective
	Inability to use tablet and the CGT app Inability to consent to study

As this is a pilot study, the sample size is determined by the number of eligible patients in the participating haemodialysis unit. While formal age-matching between the intervention and control groups is not feasible due to the small sample size, we will strive for balance in baseline characteristics through randomisation. The primary aim of this pilot study is to assess feasibility and gather preliminary data to inform a future, larger randomised controlled trial.

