### Regulatory aspects

The RCT will be conducted according to the standards of the ICH-Good Clinical Practice (GCP) and the Research Governance Framework for Health and Social Care. Pharmaco-vigilance reporting will comply with the Medicines for Human Use (Clinical Trials) Regulations 2004 and Amended Regulations 2006. Written informed consent will be provided by all patients prior to randomisation and any study-related procedures.

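### No random mechanism is specified for allocating dialysis routes to arms, yet the plan relies on randomisation for baseline balance and calls the study an RCT

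*Protocol article*

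**What the plan says.** The Randomisation section of the protocol article sets out the allocation in three steps.

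- The patient's arm follows from the schedule: "Participants will be assigned to either the intervention or control group based on their pre-existing haemodialysis schedule".
- The unit is the route, defined by day-pattern and shift: "This results in a total of six possible haemodialysis therapy routes". Everyone in a route "will be assigned to the same study arm".
- The arm of each route is left to the team: "The allocation of each route to either the intervention or control arm will be determined by the research team".

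The section qualifies the method itself: "This pseudo-randomisation method, while not truly random at the individual level, offers a pragmatic approach to group allocation". It is silent on whether chance operates at the level of the route.

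Other sections speak as if randomisation takes place. Trial population and recruitment says that formal age-matching is not feasible and that "we will strive for balance in baseline characteristics through randomisation". Regulatory aspects calls the study an RCT and states: "Written informed consent will be provided by all patients prior to randomisation and any study-related procedures". The Abstract describes it as both quasi-experimental and randomised, while Trial design says pseudo-randomised.

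Statistical analysis compares the groups by independent ANOVA and intends the results to give effect sizes for sizing the later trial. It also plans to look at schedule: "We will conduct exploratory analyses to examine potential associations between schedule and outcomes".

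**The concern.** Baseline balance is the one benefit that the plan asks of randomisation, and the Randomisation section does not supply the means to get it. A decision by the team among six known groups of patients is the only allocation step described. If that decision is in any way related to who attends each route, the relation enters the between-arm comparison, and the stated design has no later safeguard. Patients, dialysis staff and outcome assessors are all unblinded, and the between-group ANOVA names no adjustment for baseline score or route.

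At stake is the credibility of the between-arm estimate that is to be carried into the definitive trial. The feasibility, adherence and acceptability results do not depend on how arms were allocated.

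**Working it through.** The plan gives no figure on this point, so the check is mainly a comparison of its sections.

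**1. Where could chance enter?** For a patient, it cannot: the schedule already exists and fixes the route, and the route fixes the arm. For a route, the article names who decides but no draw, list, seed or independent allocator. The exact finding is that no random mechanism is specified at either level.

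**2. What depends on it?** The balance statement in Trial population and recruitment depends on it directly. The design labels in the Abstract and Regulatory aspects depend on it for their accuracy.

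**3. Does the stated order of events close the gap?** Regulatory aspects puts consent before allocation. If all consent in all routes comes first, patients are not recruited with their arm known. The team then allocates routes able to know who has consented in each, so its choice remains open to influence. If instead the order holds only patient by patient, the first allocation in a route reveals the arm of every later recruit to that route. Each reading leaves one path open.

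**4. How large could it be?** The inputs are assumptions, because the article gives no outcome SD, intraclass correlation (ICC), significance level or number of routes per arm.

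- Assume three routes per arm and route means with SD 0.2 to 0.3 of the outcome SD. The ICC is then 0.2² = 0.04 to 0.3² = 0.09.
- Ceiling: the expected mean of the top three of six standard normals minus that of the bottom three is 1.407. Multiplying gives 1.407 × 0.2 = 0.28 and 1.407 × 0.3 = 0.42 SD. This requires perfect knowledge of the route means and a deliberate choice of the best three.
- Random draw, same assumptions: expected bias is zero, but the chance difference between arms has SD √(1/3 + 1/3) = √(2/3) = 0.816 route SDs. That is 0.816 × 0.2 = 0.16 to 0.816 × 0.3 = 0.24 outcome SDs.

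**5. What would a given bias do to a test?** Assume 25 completers per arm, a two-sided 5% level and no adjustment. The standard error in SD units is √(2/25) = 0.283. For a bias of b SD, the false-positive rate is Φ(b/0.283 − 1.96) + Φ(−b/0.283 − 1.96).

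| Assumed bias (SD) | False-positive rate |
|---|---|
| 0 | 5.0% |
| 0.2 | 10.9% |
| 0.3 | 18.6% |
| 0.5 | 42.4% |

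**6. How many draws are available?** A simple 3:3 draw has C(6,3) = 20 outcomes. Pairing the two day-patterns within each shift and drawing once per pair gives 2³ = 8. Of these, 2 put each day-pattern wholly in one arm and 6 mix them.

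**The case against.** The design is disclosed. The Abstract says quasi-experimental, Trial design says pseudo-randomised, and the Randomisation section admits non-randomness at the individual level. The study is a pilot without a power calculation, and its primary outcome is worded as change within the intervention group, so stable differences in level between shifts need not carry over into change scores. All of this stands. It narrows the point to the sentences that rely on randomisation and to the between-arm comparison. That comparison is still planned, at follow-up as well as on change, and is still meant to inform a later sample size.

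A reader might infer more than the documents support:

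- *That routes are certainly not randomised.* A decision by the research team does not strictly exclude a draw, and the article condenses a fuller protocol. What can be said is that none is described.
- *That the design is concealed or misrepresented.* The open labels rule this out; the fault is inconsistency.
- *That staff will apply exclusions such as inability to use the tablet differently by arm.* Table 1 gives one set of criteria for everyone, and consent is stated to precede allocation. Differential use is conjecture.
- *That a bias of 0.28 to 0.42 SD is to be expected.* That is the ceiling under perfectly informed choice. Routes picked for convenience unrelated to outcome carry no such expected bias, and the article gives no evidence of case-mix differences between shifts.
- *That schedule and arm will be confounded.* Nothing prevents a whole day-pattern falling in one arm, which would make its association with outcome inseparable from the arm effect. But this is only a possibility, and that analysis is already labelled exploratory.

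**Conclusion.** The point holds in this form: no random mechanism is specified for patients or routes, the team that assigns each route can know who attends it, and other sections rely on randomisation and use its name. Selection bias in the between-arm comparison is therefore left open.

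That conclusion rests on the text alone. Its numerical size cannot be derived from the article. The 0.28 to 0.42 SD range bounds the expected bias only for the assumed route SD, a 3:3 split and perfectly informed choice; the false-positive rates likewise rest on assumed biases and an assumed 5% level. A random draw would remove systematic choice but would not guarantee balance with six routes.

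**What to change.** Preferred change, in the Randomisation section:

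1. Complete consent and all eligibility checks, by the same criteria, in all six routes before any route is allocated. This agrees with the order already stated in Regulatory aspects.
2. Allocate whole routes by a documented random draw, run by someone not involved in recruitment. Preferably balance by shift, so that each arm receives one of the two day-patterns for each of morning, afternoon and evening.
3. Whether also to force both day-patterns into each arm is optional. It reduces schedule confounding, but it always puts neighbouring shifts on the same days in different arms, which works against the section's aim of limiting contact between arms.

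If no draw is made, replace the randomisation and RCT wording in the Abstract, Trial population and recruitment, and Regulatory aspects with *non-randomised controlled pilot*, and report the between-arm difference as open to selection bias.

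The cost is a short text change and one draw. The team loses its free choice of routes. The 30:25 split becomes approximate: routes average 55/6 = 9.2 patients, so three per arm gives about 27 or 28 in each. Chance imbalance remains and should be acknowledged when the results are reported.
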